#### 2.5.2 Secondary observation indicators

•Vital signs such as blood pressure, heart rate, pulse oximetry saturation, blood glucose, and perfusion index.•Adverse events including local skin reactions (redness and swelling), transient neurological symptoms (headache and dizziness), gastrointestinal disturbances (nausea and vomiting), and cardiovascular effects (bradycardia and hypotension).

#### 2.5.3 Participant timeline

An overview of the study procedures is shown in Table 1.

**TABLE 1 T1:** Schedule of enrolment, interventions, and assessments.

	Study period										
	Enrollment	Allocation	Post-allocation								Close-out
Timepoint	−T1	T0	T1	T2	T3	T4	T5	T6	T7	T8	Tx
Enrollment	X										
Eligibility screen	X										
Informed consent	X										
Allocation		X									
**Intervention**											
TENS				X							
TaVNS				X							
**Assessments**											
VAS			X	X	X	X	X	X	X	X	
BIS			X	X	X	X	X	X	X	X	
MOAA/S			X	X	X	X	X	X	X	X	
Ramsay			X	X	X	X	X	X	X	X	
HRV			X	X	X	X	X	X	X	X	
Baseline			X								

## 3 Statistical analysis methods

### 3.1 Statistical methods for primary and secondary outcomes

This study will use SPSS 20.0 and PhysioZoo software for statistical analysis. The significance level of all statistical tests is set at α = 0.05, and two-sided tests are performed. For the differences in different intraoperative indicators such as pain score VAS, anesthesia depth BIS, and heart rate variability HRV between the trans-auricular vagus nerve stimulation group (taVNS group) and the transcutaneous peripheral nerve stimulation group (TENS group), an independent-samples *t*-test is first performed. If the data do not meet the normal distribution, the non-parametric test method Mann–Whitney U test will be used for comparison between the two groups. For the comparison between different subgroups (different stimulation modes) within each group, one-way analysis of variance will be performed to compare the differences in various indicators. If the data do not meet the assumptions of analysis of variance, the Kruskal–Wallis H test will be used as a non-parametric alternative method. At the same time, for multiple-measurement data, repeated-measures analysis of variance (Repeated Measures ANOVA) will be used to compare the changes of indicators at different time points within the same group. To further evaluate the impact of different influencing factors (such as stimulation mode) on intraoperative analgesia and sedation effects, multiple linear regression analysis will be used to help identify their relationships with various indicators.

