##### 2.1.4.3 Withdrawal criteria

•Deviation from the assigned anesthesia protocol.•Occurrence of any serious adverse event.•Intraoperative administration of heart rate-altering medications (e.g., atropine).•Failure to complete all required monitoring procedures.

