### 2.3 Sample size calculation

This study is a randomized controlled trial aiming to compare the effects of TENS and taVNS in foraminoscopy. According to relevant research, with the VAS as the primary outcome indicator, the standard deviation of taVNS is 2.5, and that of TENS is 3.0. Calculated using PASS software, the minimum sample size required for each group is 121. Considering a dropout rate of 10%–15%, to ensure the statistical power and the reliability of the results, the final sample size of each group is adjusted to 136 people. Each subgroup was allocated 32 participants, and a total of 272 participants are recruited.

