##### 2.4.2.1 Observation indicators

Record the changes of corresponding indicators at different time points:

•Time 1: 5 min after the patient enters the operating room, before electrical stimulation.•Time 2: Before the operation, 30 min after the electrical stimulation upon entering the room.•Time 3: Immediately at the start of the operation.•Time 4: 0.5 h after the start of the operation.•Time 5: 1.0 h after the start of the operation.•Time 6: 1.5 h after the start of the operation.•Time 7: 2.0 h after the start of the operation.•Time 8: At the end of the operation.

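### No named between-group test uses the T1 baseline, repeated-measures ANOVA stays within groups, and time points falling after the end of surgery have no rule

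*Protocol article*

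**What the plan says.** All points are in the protocol article.

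- **Between groups (3.1).** VAS, BIS and HRV are compared between TENS and taVNS by independent-samples t-test, or by Mann–Whitney if not normal. No baseline term and no time point is named.
- **Between modes (3.1).** "For the comparison between different subgroups (different stimulation modes) within each group, one-way analysis of variance will be performed", with Kruskal–Wallis as the fallback.
- **Over time (3.1).** Repeated-measures ANOVA "will be used to compare the changes of indicators at different time points within the same group".
- **Regression (3.1).** A multiple linear regression is planned on influencing factors. Stimulation mode is given as the example; no other factor is named.
- **Schedule (2.4.2.1 and Table 1).** T1 precedes stimulation. T4 to T7 are at 0.5, 1.0, 1.5 and 2.0 h from the start of the operation (the last is "Time 7: 2.0 h after the start of the operation"), and T8 is its end. Table 1 marks VAS, BIS, MOAA/S, Ramsay and HRV at every one of T1 to T8.
- **Missing data (3.3 and 2.4.2.1.1).** Intention-to-treat is promised, with missing data handled according to guidelines. Recent data are used for patients who withdraw or find the analgesia unsatisfactory.
- **Additional analyses (3.2).** None are planned.

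**The concern.** Three features of the analysis do not fit the data being collected.

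First, each main outcome has a pre-stimulation value, yet no named between-group test uses it. The cost is precision.

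Second, the only longitudinal method runs inside each group. It can show that a group changed, but not that two groups changed differently. Section 3.5 expects a clearer HRV effect with taVNS and a non-significant one with TENS. If that pattern is read from two separate within-group tests, it says nothing reliable about the difference. The mode comparison is split in the same way: the 2 × 4 layout of site by mode becomes two separate one-way analyses, and no named test compares modes across sites.

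Third, a patient whose operation ends before 2.0 h has no T7, and one whose operation ends before 1.5 h has neither T6 nor T7. A classical repeated-measures ANOVA on complete cases would leave such patients out. Those who remain would be selected by operation length, which is determined after randomisation and may be related to pain and cooperation.

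**Working it through.** **1. The plan's own figure.** Section 2.3 sizes the trial "with the VAS as the primary outcome indicator, the standard deviation of taVNS is 2.5, and that of TENS is 3.0" and states that "Calculated using PASS software, the minimum sample size required for each group is 121". Section 3.1 adds: "The significance level of all statistical tests is set at α = 0.05, and two-sided tests are performed". The mean difference and the power are not given, so I assume 1.0 point and 80%.

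- Normal formula: n = (1.960 + 0.842)² × (2.5² + 3.0²) / 1.0² = 7.849 × 15.25 = 119.7, so 120.
- Welch t-test: n = 120 gives power 0.798 and n = 121 gives 0.801, so 121.

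The stated 121 is therefore consistent with an unadjusted two-group comparison under these two assumptions. At 90% power, 121 would instead imply a difference of 1.151.

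**2. Gain from adjusting for T1.** With correlation rho between T1 and the analysed value, the residual variance is multiplied by 1 − rho². The required n is 119.7 × (1 − rho²), rounded up. Power at 121 per group is Φ(√(121 / [15.25 × (1 − rho²)]) − 1.96).

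| rho (assumed) | variance removed | n per group | power at 121 |
|---|---|---|---|
| 0 | 0% | 120 | 0.80 |
| 0.2 | 4% | 115 | 0.82 |
| 0.3 | 9% | 109 | 0.84 |
| 0.5 | 25% | 90 | 0.90 |

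The document gives no rho. It may be low: T1 VAS is taken before surgical pain, and the T1 sedation measures are taken in conscious patients, probably with little spread.

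**3. Reading two within-group tests against each other.** Suppose both groups change by exactly the same amount and each within-group test has power p. The chance that one test is significant and the other is not is 2p(1 − p):

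- p = 0.3: 0.42
- p = 0.5: 0.50
- p = 0.8: 0.32

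So a split result would appear in about a third to a half of trials with no difference between groups. This result does not depend on rho.

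**4. Times after the end of surgery.** No operation times are given. If a share f of patients reaches T7 and only complete cases were analysed, 121 per group becomes 121 × f. The power shown is for a two-group contrast of 1.0 point on those patients.

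| f (assumed) | n per group | power |
|---|---|---|
| 80% | 97 | 0.71 |
| 60% | 73 | 0.59 |
| 40% | 48 | 0.43 |
| 20% | 24 | 0.24 |

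These rows show what would follow from complete-case analysis. They do not describe a planned loss.

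**5. Why the site contrast should use active cells.** Each group has three energised modes and one unenergised control. With equal cells and no site difference among controls, a site effect averaged over all four cells is 3/4 of the active-cell difference. A true difference of 1.0 would appear as 0.75.

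**The case against.** The case on the other side is substantial, and it limits the point in five ways.

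- **Validity.** In a randomised trial the unadjusted t-test is unbiased. Leaving out T1 costs precision only, and if rho is near zero it costs almost nothing. This stands.
- **Each time point tested.** A reader might infer a separate test at every time point. Section 3.1 names none; the supportable criticism is that the tested quantity is undefined.
- **Patients dropped or withdrawn.** A reader might infer that patients with short operations are deleted, or that they meet the withdrawal criterion "Failure to complete all required monitoring procedures". The document says neither. Sections 3.3 and 2.4.2.1.1 promise intention-to-treat and some handling of missing data, and a reading at 2.0 h is not naturally required once the operation is over. What remains is that no stated rule covers values that do not exist.
- **No model across sites, T1 wasted.** The regression in 3.1 is open enough to include site or baseline, and T1 can enter the within-group ANOVA. Only the named between-group tests leave T1 out.
- **Within-arm inference planned.** Section 3.1 also compares groups directly and nowhere says that within-group p-values will be set against each other. The expectation in section 3.5 makes that reading a real risk, but not a stated method.

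None of this supplies a group-by-time comparison. Section 3.1 assigns repeated-measures ANOVA to within-group change explicitly, so this is not simply a detail left to an unseen analysis plan.

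**Conclusion.** The point holds in this limited form. Section 3.1 names no baseline-adjusted between-group test and plans no group-by-time comparison, and the document has no rule for scheduled times that fall after the end of surgery. The planned two-group test is valid but less precise than the collected data allow.

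The precision gain is illustrative and rests on an assumed rho: 0–4% of variance at rho 0–0.2, 9% at 0.3 and 25% at 0.5. The power figures also assume a 1.0-point difference. The within-arm problem and the undefined time points do not depend on rho, but the number of patients affected by the latter cannot be estimated from the document. This is a change that should be made, at little cost; it is not a flaw that invalidates the trial.

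**What to change.** Rewrite section 3.1 as follows.

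- **VAS, BIS, HRV.** Replace the unadjusted tests and the within-group ANOVA with a linear mixed model per outcome, using all available post-baseline values. Include the T1 value as covariate; site, mode, time and their interactions as fixed effects; and patient as random effect.
- **TENS vs taVNS.** Estimate it as a contrast among the active-stimulation cells, at a named time point or as a named time-average. Report the sham contrasts separately.
- **MOAA/S and Ramsay.** Use an ordinal model or keep rank-based tests. A Gaussian model does not suit these scales.
- **Times after the end of surgery.** Define them as not applicable rather than missing, and state that they are not a failure of monitoring. The model does not remove selection by operation length at T6 and T7, so the named time point should be one that nearly all operations reach.

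The cost is a rewrite of one section. No extra data or patients are needed, and the mixed model can be fitted in SPSS, which the plan already names.

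### No between-mode analysis in Section 3.1 has a patient term, although each outcome is read up to six times per patient during surgery

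*Protocol article*

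**What the plan says.** Section 3.1 names four kinds of analysis for the repeatedly measured indicators.

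- TENS against taVNS: independent-samples t-test, with Mann–Whitney as fallback.
- Stimulation modes within each device group: "one-way analysis of variance will be performed to compare the differences in various indicators", with Kruskal–Wallis as fallback.
- Repeated-measures ANOVA, whose stated use is to "compare the changes of indicators at different time points within the same group".
- Regression, introduced with the purpose "To further evaluate the impact of different influencing factors (such as stimulation mode) on intraoperative analgesia and sedation effects", after which "multiple linear regression analysis will be used to help identify their relationships with various indicators". No fallback is given here.

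Section 2.4.2.1 gives the instruction "Record the changes of corresponding indicators at different time points" and lists eight times. The readings in surgery run from "Time 3: Immediately at the start of the operation" to "Time 8: At the end of the operation", so there are at most six. Table 1 schedules VAS, BIS, MOAA/S, Ramsay and HRV at all eight times.

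**The concern.** The article recognises that the data are repeated, but applies a method for repeated data only to the question of change within a group. Stimulation mode varies between patients. For a between-patient factor, positive correlation among one patient's readings means that six readings carry less information than six patients. A model with one error term and no patient term ignores this if each reading is a row, and its standard error for mode is then too small. If only one reading per patient enters, the test is valid but gives up information that the trial has collected.

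Comparing the waveforms and optimising the stimulation parameters are stated aims (end of the Introduction, Section 2.4.1). Section 3.5 already predicts that the dense-sparse wave will show the clearer changes. The regression is also the only named method that could estimate mode across both devices together, because the ANOVA is run within each device group.

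**Working it through.** The plan gives no figure on this point to reproduce: it states no within-patient correlation and no unit of analysis for the regression.

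**Inputs**
- Readings in surgery: T3 to T8, so m = 6 at most (Section 2.4.2.1, Table 1).
- Two-sided alpha of 0.05 (Section 3.1).
- Patients per mode across both devices: 272/8 = 34 per cell, 2 × 34 = 68. Section 2.3 also states 32 per subgroup, and 8 × 32 = 256, not 272. The choice hardly matters here, because the error rates depend on m and the correlation.
- Within-patient correlation ρ: assumed, equal between all pairs of readings, range 0.1 to 0.7.

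**If the readings were stacked as rows**

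The true variance of a mode contrast exceeds the reported one by the design effect DE = 1 + (m − 1)ρ. The true type I error of one contrast is 2 × [1 − Φ(1.96/√DE)]. The omnibus four-mode test was simulated under no effect (4,000 trials per setting, 4 modes × 68 patients × 6 readings).

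| ρ | DE (m = 6) | One contrast | Omnibus, stacked | Omnibus, per-patient mean |
|---|---|---|---|---|
| 0.1 | 1 + 5 × 0.1 = 1.5 | 11.0% | 15% | 4.9% |
| 0.3 | 1 + 5 × 0.3 = 2.5 | 21.5% | 37% | 5.2% |
| 0.5 | 1 + 5 × 0.5 = 3.5 | 29.5% | 54% | 5.2% |
| 0.7 | 1 + 5 × 0.7 = 4.5 | 35.6% | 63% | 5.2% |

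For example, at ρ = 0.3, 1.96/√2.5 = 1.24, and the two-sided tail beyond 1.24 is 21.5%.

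Shorter operations yield fewer readings. With m = 4, DE is 1.9, 2.5 and 3.1 at ρ = 0.3, 0.5 and 0.7, and the single-contrast error is 15.5%, 21.5% and 26.6%.

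**If a single reading were used**

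The variance of the six-reading mean relative to one reading is (1 + 5ρ)/6:
- ρ = 0.3: 2.5/6 = 0.417, so 58% of the information is lost.
- ρ = 0.5: 3.5/6 = 0.583, so 42% is lost.
- ρ = 0.7: 4.5/6 = 0.75, so 25% is lost.

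The loss exceeds half only when (1 + 5ρ)/6 < 0.5, that is, when ρ < 0.4.

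To illustrate in power: take one mode against control (68 v 68), an assumed VAS difference of 1.0, and SD √((2.5² + 3.0²)/2) = 2.76 from Section 2.3, read as the SD of one reading. Power is 56% with one reading, and 91%, 79% and 68% with the mean of six at ρ = 0.3, 0.5 and 0.7.

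**The case against.** The strongest reply is that the article makes no wrong statement about the regression. It never says that readings are stacked or that one time point is picked, and its separate treatment of repeated data shows that the authors know the readings are correlated. A mean or area under the curve per patient fits the stated regression and holds the 5% level. Such detail is commonly left to an analysis plan, which is not shown. The direct comparison of modes is the one-way ANOVA, and the regression is a supplement.

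Much of this stands. A reader might infer that the plan will stack the readings and so run at a 37% to 63% false-positive rate; the text does not support that, and those figures are conditional. A reader might also infer that a single reading would waste most of the data. Five of six readings is most by count, but most of the information is lost only for ρ below 0.4. Nor is the regression the main test of mode.

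What remains is more than silence. Section 3.1 assigns its repeated-measures method to within-group change only, and no between-mode or between-device method that it names accounts for within-patient correlation. The ANOVA and the t-test name no time point either, so the gap extends to them.

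On sedation, "on intraoperative analgesia and sedation effects" does not name MOAA/S or Ramsay as regression outcomes, so the concern about a linear model for ordinal scales applies only if they are analysed that way.

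**Conclusion.** The point holds as a weakness in the method that is named, not as a proven error in the results. The size depends on a choice that the article leaves open. Stacking would raise the type I error of one mode contrast to about 21.5% to 35.6%, and of the omnibus test to about 37% to 63%, for ρ from 0.3 to 0.7. A single reading would keep the 5% level but lose 58% to 25% of the information over the same range. A per-patient mean would avoid both problems. These figures assume six readings for every patient, equal correlation between readings, and values of ρ that the documents do not supply. The change is worth making because a better method is available at little cost.

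**What to change.** In Section 3.1, replace the multiple linear regression, for the between-mode and between-site evaluation, by a linear mixed model for each indicator. Use all available T3 to T8 readings, a patient random effect, and fixed effects for site (auricular or acupoint), mode, time and the T1 value, which is taken before stimulation. This model also accommodates short operations with no late readings.

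An acceptable simpler alternative is to keep the linear regression on one pre-named per-patient summary, such as the mean of the intraoperative readings, adjusted for T1. If the t-test and ANOVA are kept, they should name the reading or summary that they use. If MOAA/S and Ramsay are analysed this way, use an ordinal model, by GEE or with a patient random effect.

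The cost is a change of wording and a little more analysis work; SPSS has mixed-model and GEE procedures. Standard errors will be wider than stacked rows would give. No change to recruitment or data collection is needed.

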### 3.2 Methods for additional analyses

There are currently no plans for additional data analysis.

### 3.3 Methods in analysis to handle protocol non–adherence and any statistical methods to handle missing data

Intention-to-treat analysis will be used, and missing data will be appropriately processed in accordance with established guidelines.

### 3.4 Interim analyses

No interim analysis is planned.

### 3.5 Expected results

The expected research results are that taVNS may exert sedative effects and potentially reduce the use of adjuvant analgesic drugs and has a positive effect on the relevant indicators of heart rate variability, which is a new and effective anesthesia-assisting method during foraminoscopy. The specific manifestations are as follows: 1. The taVNS group has a more obvious analgesic effect (the VAS score increases more significantly), a more obvious impact on the relevant indicators of HRV (the standard deviation of heart rate increases, RMSSD and SDNN decrease, and LF increases), a lower BIS value, and a significant reduction in the additional amount of oliceridine fumarate for patients compared with the TENS group. This indicates that the regulatory role of the vagus nerve plays an important role in pain regulation, and taVNS enhances the activity of the parasympathetic nerve, making the depth of anesthesia more stable; 2. TENS has a certain analgesic effect, but its impact on HRV is not significant; 3. Among different stimulation modes, the dense-sparse wave group (sparse wave 6 Hz, dense wave 30 Hz) has more obvious changes in HRV, VAS, BIS, and sedation under the parameters of 30 Hz and 200-pulse width. At the same time, by using the Huatuo brand electronic diagnosis and treatment instrument SDZ-IIB, a more effective and safer stimulation mode for the sedative and analgesic effects of patients can be obtained, providing more simple and effective treatment guidance for patients.

## 4 Discussion

HRV refers to the variation in time intervals between consecutive heartbeats and is mainly controlled by the cardiac autonomic nerves. It has been widely recognized as an effective indicator for evaluating autonomic nerve function.

The application of TENS and taVNS represents an emerging analgesic, sedative, and neuromodulatory strategy during foraminoscopy. These two non-pharmacological, minimally invasive modulation techniques are considered potentially beneficial for optimizing perioperative management, though their effects require cautious evaluation. Both modalities deliver electrical currents via stimulators, constituting a primary source of electromagnetic interference. Consequently, they are contraindicated in patients with implantable cardioverter defibrillators (ICDs), with interference levels demonstrating significant correlation to stimulation parameters that necessitate strict control (28). Additionally, substantial challenges exist in parameter selection due to individual variability in:neural sensitivity to stimulation, stimulation tolerance thresholds, psychological factors. Electrode placement for TENS should avoid surgical fields to prevent contamination. Notably, high-quality clinical studies investigating TENS and taVNS applications during MAC for transforaminal endoscopy remain limited. This study aims to provide novel clinical data in this domain.

Some studies have shown that a higher HRV is usually associated with a healthy state, stronger adaptability, and a lower disease risk (29); while a lower HRV is related to anxiety, stress, cardiovascular diseases, etc (24). In addition, Billman (30) found that HRV is also related to the body’s stress response, and the cardiac parasympathetic nerve activity is the main part of HRV. In this paper, the regulation of cardiac vagus nerve and parasympathetic nerve is quantitatively and dynamically evaluated by analyzing the frequency domain, time domain, and non-linear analysis methods of HRV. The VAS is a commonly used subjective assessment tool, which is widely used for various subjective experiences such as pain and anxiety. By using HRV and VAS together, this study comprehensively evaluates the intervention effect from both physiological and psychological dimensions. The BIS value is an important tool for assessing the depth of anesthesia during the operation. Together with the sedation scale (MOAA/S) and Ramsay sedation scale, the intraoperative state of patients can be evaluated in detail to ensure efficient evaluation.

This study explored the differences in the curative effects of TENS and taVNS in monitored anesthesia during foraminoscopy. The results of the study are expected to show that transcutaneous electrical nerve stimulation not only has a certain effect on sedation and analgesia, but also can reduce the use of auxiliary analgesic drugs and has a positive effect on the indexes of HRV, which is a new and effective anesthesia auxiliary modality in intervertebral foraminoscopy. The specific performance is as follows: 1. The taVNS group has a more obvious analgesic effect than percutaneous peripheral nerve stimulation, a more obvious effect on the relevant indexes of HRV (increase in the standard deviation of heart rate, increase in RMSSD, decrease in SDNN, and increase in LF), a significant decrease in the LF/HF ratio by taVNS, a change in the autonomic balance of the heart to a parasympathetic/vagal dominance, a significant decrease in the patient’s response to oxalidine fumarate, and a significant decrease in the amount of additional drugs, which can be shown to be a new and effective anesthetic aid in intervertebral foraminoscopy. The additional amount was significantly reduced, which can indicate that the modulation of vagus nerve plays an important role in pain modulation, and the taVNS enhanced the activity of parasympathetic nerves and stabilized the depth of anesthesia; 2. TENS had a certain analgesic effect, but its effect in HRV was not significant; 3. In different stimulation modes, the dense-sparse wave group (sparse wave 6 Hz-dense wave 30 Hz). Among the different stimulation modes, the sparse-dense wave group (sparse wave 6 Hz-dense wave 30 Hz) had more obvious changes in HRV, VAS, BIS, and sedation under the parameters of 30 Hz and 200 pulse width. At the same time, by using the electronic diagnostic instrument SDZ-IIB, it is possible to derive more effective and safer stimulation modes for patients’ sedation and analgesia, and to provide patients with simpler and more effective therapeutic guidance.

Previous studies in related fields have shown that taVNS has a positive impact on patients’ sedation and analgesia, heart rate variability, etc., and at the same time reduces the use of opioids (31). TENS may have a more obvious local analgesic effect, but its impact on heart rate variability is relatively limited. Parseliunas et al. (32) studied that TENS is of great significance in relieving postoperative pain after inguinal hernia repair, which is consistent with the expected results of this study. However, some studies have different conclusions. Gibson et al. (33) found that there is not enough evidence for the therapeutic effect of TENS on neuropathic pain in adults. These differences may be related to differences in experimental design, electrical stimulation parameters, sample characteristics, etc.

